#### 2.4.4. Covariates

Demographic information on parental educational level, ethnicity, and household constitution is assessed through the questionnaire at the baseline interview. Both anthropometrics, ethnicity, and parental educational level, are compared with data from Hvidovre municipality to assess generalisability.

#### 2.4.5. Development and Validation of the Questionnaire

Previously validated questionnaires were used as described when relevant. The questionnaire was discussed in the research group to ensure coverage of relevant disciplines. One external expert on family life styles further revised questions on family activities. Face validity was tested with six parents in individual online think-aloud interviews in a pilot test. Think-aloud interviews were used to ensure that the questions were understandable and understood in the same manner across interviews. For example, the interviewer asked questions such as, *how do you understand this question?* Questions with more than one interpretation were removed from the questionnaire or specified in a more detailed manner. Time consumption and feasibility were further tested in a field test with 26 parents with children aged 4–9 years.

### 2.5. Process-Evaluation

A mixed method approach will be used to evaluate compliance as well as the feasibility and acceptability of the intervention. Fetters et al. states the default expectation for conducting interventional studies should be a combination of qualitative and quantitative components [52]. The evaluation will help understand how and why the intervention, or parts of it, was effective or ineffective and whether the intervention holds the potential to be successful in a wider context.

Quantitative measures will include questions in the post-intervention questionnaire on the number and kinds of activities participants have knowledge of, have tested, and are satisfied with, e.g., how many times the family played the card game. Further, participants will be asked to evaluate the usability of the main messages of the project. Open-ended questions will be included where participants are invited to voice their opinions and experiences. Finally, participants will be asked whether they would recommend the use of the various intervention components to others. With regard to the participants in the control group, they will receive additional questions related only to the health nurse consultation. Regarding the evaluation of the use of a social media platform (Facebook), different metrics will be used to measure volume of engagement, i.e., number of “likes”, total comments, and comments on sharing experiences. Engagement will be evaluated separately for different categories of posts.

Semi-structured qualitative interviews will be conducted post-intervention with 20 families from the intervention group in order to get a more in-depth evaluation of the intervention components and a better understanding of e.g., the motivators and barriers, compliance and food and activity habit changes made by the families. In addition, 2–3 focus groups will be conducted among the school health nurses having had consultations with either intervention or control families to evaluate intervention delivery at the consultation, suggestions for intervention component improvements and their views on future perspectives and possibilities for disseminating nation-wide. All interviews will be transcribed and coded into themes by the interviewer using the framework of content analysis [53].

Hvidovre municipality is affected by the COVID-19 epidemic with several school classes closing for one or several weeks with short notice. Information on infections and closed school classes will be collected as dietary habits and compliance to the intervention might be affected by the situation.

### 2.6. Pilot Study

A pilot study was carried out to assess measurement procedures, questionnaires and other data collection instruments, logistics and suitability of the intervention components for the target age group. Due to the Covid-19 context, the pilot study had to (1) be postponed from May 2020 to August 2020 and (2) reduced from six weeks to four weeks. The compressed procedure taken into account the follow-up measurements were omitted. Eight 1st grade children and their parents participated in the pilot study. All eight families completed all intervention components, but the measurement of pre-post differences. The test thus comprised an evaluation of the questionnaire, the 7-day dietary record, the sugar-rich food screener, the consultation with school health nurse, the take-home box as well as a communication and social media platform. Materials were well received among both school health nurses, parents, and children following minor adjustments, primarily related to the design and phrasing in the inspiration booklet, and rules in the game to be easier to understand. Parents stressed how the consultation and the material from the take-home box jointly and in synergy provided a vehicle for behaviour change. Consequently, the pilot study provided useful and relevant data on practicality, sensitivity, and suitability of materials.

### 2.7. Statistical Considerations

Primary analysis will focus on testing the effectiveness of the intervention, by analysing the change in intake discretionary food and drinks from baseline to the 3.5-month follow-up between intervention and control groups. Changes in intake of discretionary foods and drinks will be expressed in absolute changes (kJ/d) and in relative changes as kJ/10 MJ. Changes in food groups and sub-groups (e.g., chocolate, cakes or ice-cream), will also be evaluated in g/d.

Linear mixed models will be used with discretionary food and drinks as a combined variable, and sugar-rich discretionary food and discretionary drinks separately as outcome variables. Group (intervention or control) baseline intake of discretionary food and discretionary drinks will be analysed as a fixed effect and school as a random effect as there has been a cluster randomisation on school level. Primary outcome will be calculated using intention-to-treat analysis, including all participants irrespective of adherence or dropouts. Missing data will be imputed using multiple imputation. Sensitivity analysis will be performed with complete case analysis, and per protocol analysis, where analysis will be carried out for participants that (1) complete the sugar-rich food screener and health consultation; (2) report to play the card game and used at least one other item from the box. Further, sensitivity analysis will likewise be used to test the effect of having twins or triplets in the intervention.

Adjustment for group imbalances and potential confounders such as parental education, BMI and physical activity will be performed for both primary and secondary outcomes. Estimates of the effect size will be presented along with 95% confidence intervals and p-values. The significance level is set at 5%. Statistical analysis will be carried out using R version 4.0.

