## Abstract

A high consumption of sugar-rich discretionary food and drinks has several health implications, which have been traced from childhood into adulthood. Parents act as primary mediators shaping children’s dietary habits, and interventions that engage parents have shown to result in positive outcomes. Further, collaboration with local school health nurses and dentists provides an effective structural frame to support behaviour change and anchor new initiatives. The multicomponent 3.5-month cluster randomised family-focused intervention “Are you too Sweet?” aims to evaluate the effectiveness of communicating new Danish guidelines for sugar-rich discretionary food and drinks for school starters (5–7 years). This paper describes the development, outcomes and process evaluation of the intervention that includes three main components: extended dialogue during a school health nurse consultation, a box with home-use materials, and a social media platform to facilitate interaction among participants. Children (*n* = 160) and their parents were scheduled for a baseline interview at six different schools. The intervention was developed to increase self-efficacy, knowledge about guidelines, observational learning and reduce impediments for behavioural change. The desired primary outcome was a reduction in intake of sugar-rich food measured through a 7-day dietary record. The results contribute to the evidence on effective health promotion strategies.

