#### 2.2.1. Study Population and Sample Size

Eligible children are children starting public pre-school education at six chosen schools in Hvidovre municipality in August 2020. There is no inclusion criteria regarding diet or disease. Power calculations were performed based on 6–7 year-old children from the Danish National Survey of Diet and Physical Activity [28]. Calculations determined that 76 participants will be needed in both intervention and control groups to detect a 25% reduction in the intake of sugar-rich discretionary foods at a power of 80% and a 95% confidence interval. For a 25% reduction in intake of added sugar, 63 participants will be needed. To account for dropouts or loss of participants to follow-up, an enrolment of a minimum of 100 families in the intervention group and an additional 100 families in the control group was planned.

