#### 2.3.1. New Guidelines

As a foundation for the intervention, new guidelines for maximum intake of discretionary food and drinks were developed. We developed a model on nutritional profiling to classify foods regarded as discretionary foods. In this model, foods and drinks were evaluated based on 20 different qualifying nutrients, four disqualifying nutrients, and the energy density. The foods regarded as discretionary foods, calculated from the model consisted of sugar-rich foods (cakes, confectionary, ice cream and chocolate), energy-dense snacks (energy-bars, crackers and chips) and discretionary drinks (SSBs, fruit drink concentrate and artificially sweetened beverages). The amount of energy for discretionary food and drinks choices in a healthy diet was calculated for two age groups, 4–6 years and 7–9 years. For this calculation, the average Danish diet in each age/gender group was modelled to meet nutritional requirements (RI) as well as official Danish dietary guidelines. Thus, the modelled diet is healthier than an average Danish diet. The amount of discretionary food and drinks is communicated as serving sizes corresponding to 450 kJ. The maximum intake advised for 4–6 years, and for 7–9 years of pre-defined discretionary food was four and five servings per week, respectively.

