### 2.4. Outcomes

#### 2.4.1. Primary Outcomes

The primary outcomes are changes in intake of pre-defined discretionary food and drinks measured by dietary assessment at baseline and a 3.5-month follow-up. Discretionary food are categorised as described in Section 2.3.1, and daily consumption are summarised for each participant.

Dietary assessment will be carried out using a web-based, 7-day dietary record. Parents are instructed at the baseline interview to fill out the dietary record on behalf of their child. A similar web-based dietary assessment software has been validated for children 8–11 years [38]. The dietary assessment software is structured by six eating occasions a day, breakfast, lunch and dinner, and three in-between meals after breakfast, after lunch and after dinner. For each meal, participants can search for food items, and choose between portion sizes among 1–4 different pictures for each item. If food items cannot be found, there is an option to add an open answer. Further, participants are reminded to register related food items such as spread (for bread) or milk (on cereals) and they are separately reminded to register drinks. For each meal, they are asked questions about where they had the meal, and whom they ate together with. Finally, participants are asked if they forgot to register sweets or chocolate, if they had any supplements, and if the day represented a usual or an unusual day and reasons such as birthday or illness. If parents fail to register for a day, they will be reminded by e-mail the following day, and receive a text message after two days of missing registrations.

Intake of food items, energy and nutrients are calculated for each study participant for each meal and as an average intake per day using the software system General Intake Estimation System (GIES) version 1.000.i6 and the Danish Food Composition Databank version 7.0, both developed at the National Food Institute, Technical University of Denmark. Mis-reporters of dietary intake are identified by evaluating reported energy intake using the Goldberg cut-offs for the ration between reported energy intake and estimated basal metabolic rate at individual level (BMR) as suggested by Black [39]. BMR will be calculated using gender-specific equations [40,41] with use of weight and height measured by school health nurses. At least four days including one weekend day have to be completed for an individual to be included in the analysis.

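### The article does not fix one primary variable and scale: the abstract, sample size, outcome section and analysis section each describe it differently

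*Protocol article*

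**What the plan says.** Four places in the protocol article bear on the primary outcome.

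- **Abstract:** "The desired primary outcome was a reduction in intake of sugar-rich food measured through a 7-day dietary record". Drinks are not mentioned and no unit is given.
- **2.2.1, sample size:** 76 per group to detect a "25% reduction in the intake of sugar-rich discretionary foods", with 80% power and 95% confidence. A second figure, 63, is for a 25% reduction in added sugar, which 2.4.2 lists as a secondary outcome.
- **Outcome section (2.4.1):** "The primary outcomes are changes in intake of pre-defined discretionary food and drinks measured by dietary assessment". The outcomes are plural and cover food and drinks.
- **2.7, analysis:** the section opens by describing the primary analysis as the change in discretionary food and drinks between groups. Changes are to be "expressed in absolute changes (kJ/d) and in relative changes as kJ/10 MJ". It then says: "Linear mixed models will be used with discretionary food and drinks as a combined variable, and sugar-rich discretionary food and discretionary drinks separately". It later refers to the primary outcome in the singular without saying which variable or scale is meant, and sets one 5% significance level.

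Section 2.3.1 supplies the definitions. The discretionary category "consisted of sugar-rich foods (cakes, confectionary, ice cream and chocolate), energy-dense snacks (energy-bars, crackers and chips) and discretionary drinks". Sugar-rich foods are therefore one of three classes.

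**The concern.** A trial's effectiveness claim should rest on one variable on one scale, chosen before the data are seen, or on several with the error rate shared among them. Here a reader cannot tell which result decides the trial. It could be the combined variable, sugar-rich food alone or drinks alone, and it could be read in absolute or energy-adjusted terms.

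The choice of scale can matter. Section 2.4.2 allows that discretionary food may be eaten as excess energy, so total energy may change. If it does, kJ/d and kJ/10 MJ can give different answers.

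Two things are at stake. If whichever result is favourable may be presented as the primary finding, the nominal 5% does not hold. And if the sample size was computed for a narrower variable than the one analysed, the stated 80% power does not describe the primary comparison. The Discussion says the statistical considerations were set out to avoid data-driven analysis. That aim needs the primary variable and scale to be fixed.

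**Working it through.** **1. The wording side by side**

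| Place | Variable | Scale |
|---|---|---|
| Abstract | sugar-rich food | none given |
| 2.2.1 | sugar-rich discretionary foods; also added sugar | none given |
| 2.4.1 | discretionary food and drinks (plural outcomes) | none given |
| 2.7, opening | discretionary food and drinks | kJ/d and kJ/10 MJ |
| 2.7, models | combined; sugar-rich food; drinks | not stated per model |

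Section 2.4.1 and the opening of 2.7 agree. The abstract, 2.2.1 and the list of models do not match them. Energy-dense snacks belong to the category in 2.3.1 but appear in neither separate model, so the two named parts do not add up to the combined variable.

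**2. The plan's own sample size**

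The article gives no mean or SD, so 76 and 63 cannot be reproduced independently. They can only be solved backwards. I use two-sided 5%, 80% power, equal groups and no clustering term:

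n per group = 2 × (1.960 + 0.842)² × (CV / 0.25)², so CV = 0.25 × √(n/2) / 2.802, where CV is SD/mean.

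- n = 76: CV = 0.25 × 6.164 / 2.802 = 0.550 (standardised effect 0.25/0.550 = 0.45).
- n = 63: CV = 0.25 × 5.612 / 2.802 = 0.501 (standardised effect 0.50).

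These values do not show which variable the survey figures described.

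**3. Chance of at least one false positive**

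Under independence, with each test at 5%:

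- three tests: 1 − 0.95³ = 14.3%
- six tests (3 variables × 2 scales): 1 − 0.95⁶ = 26.5%

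The tests are not independent, so I simulated their structure (1,000,000 draws per setting). Food and drinks statistics have correlation ρ. The combined statistic is (F + wD) / √(1 + w² + 2ρw), where w is the ratio of drinks SD to food SD. The second scale has correlation r with the first. A test rejects when |Z| > 1.96. The values of ρ, w and r are assumptions, because the article gives none, and snacks are left out of the combined variable for simplicity.

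| ρ | w | 3 variables, one scale | 6 tests, r = 0.95 | 6 tests, r = 0.8 |
|---|---|---|---|---|
| 0 | 0.5 | 11.2% | 14.2% | 17.0% |
| 0 | 1 | 11.5% | 14.6% | 17.3% |
| 0.3 | 0.5 | 10.4% | 13.2% | 15.8% |
| 0.3 | 1 | 10.5% | 13.4% | 16.0% |
| 0.5 | 0.5 | 9.6% | 12.2% | 14.6% |
| 0.5 | 1 | 9.6% | 12.4% | 14.7% |

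**4. Cost of keeping every variable primary**

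With CV = 0.550 and a Bonferroni split, n per group = 2 × (z + 0.842)² × (0.550/0.25)² = 9.68 × (z + 0.842)².

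- Three tests (z = 2.394): 102 per group; power at 76 falls from 80% to 65.8%.
- Six tests (z = 2.638): 118 per group; power at 76 is 56.5%.

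The article reports 160 children scheduled at baseline in total, so naming one primary variable costs far less than splitting the 5%.

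**The case against.** The strongest reply is that the plan already has a primary variable. Section 2.4.1 and the first sentence of 2.7 both point to discretionary food and drinks together, and the combined variable comes first in the list of models. This largely stands, and it is why the fix selects that variable. It does not settle the scale, the plural in 2.4.1, or the wording of the abstract and 2.2.1.

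A reader might infer more than the article supports in five ways.

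- **Six primary tests, each at 5%.** The article does not say this. No sentence calls the separate food and drinks models primary, and the sentence on scales does not say that both apply to all three models. The six-test figure is conditional on that reading.
- **An error rate of 26%.** This requires independent tests. The combined variable contains the other two, and kJ/10 MJ is the same intake rescaled by total energy.
- **A missing multiplicity rule.** An analysis plan not shown may contain one, so its absence from an article is not the finding. The finding is that the article names the primary variable inconsistently.
- **A proven mismatch between power and outcome.** The article sometimes uses sugar-rich loosely: its sugar-rich food screener (2.3.2) records all pre-defined discretionary food and drinks. The term in 2.2.1 may be shorthand. Against that, 2.3.1 defines sugar-rich foods as a subclass and 2.7 models them apart from drinks. The point is unresolved.
- **A flaw in measuring drinks in kJ because the class includes artificially sweetened beverages.** This relies on an energy content that the article does not give. The guideline itself works in energy (450 kJ servings), and 2.7 already plans food groups in g/d.

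**Conclusion.** The concern holds as an inconsistency within the article: it does not commit to one primary variable on one scale. If any of the listed results could carry the claim, the false-positive chance is about 10 to 11% for three variables on one scale (9.6% to 11.5% across the settings tried). It is about 12 to 17% if both scales apply to all three. That is roughly two to three and a half times the nominal 5%. The ranges rest on assumed food-drink correlations of 0 to 0.5, drinks-to-food SD ratios of 0.5 to 1 and between-scale correlations of 0.8 to 0.95.

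Under the article's own definitions the variable behind the 76 is narrower than the outcome in 2.4.1, but only the authors can say whether that wording was meant literally.

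**What to change.** 1. In 2.4.1 and 2.7, name combined discretionary food and drinks as the single primary variable.
2. Have the authors choose one scale, kJ/d or kJ/10 MJ, and record the choice before follow-up data are analysed. The article gives no ground for preferring either.
3. Label the other scale, sugar-rich food and drinks as secondary or supportive, so that none can establish effectiveness alone.
4. Align the abstract and 2.2.1 with this. State whether the 76 per group refers to the combined variable. If it does not, restate the detectable difference for that variable from the survey data already used.

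The cost is wording in four places, possibly one short recalculation, and the acceptance that only one comparison can carry the primary claim. With one variable on one scale the error rate returns to 5%. The 76 then needs no multiplicity correction, provided it was computed for that variable.

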### 2.8. Consent to Participate and Ethics

As the intervention is non-invasive, the local ethics committee confirmed that no official approval is needed (journal-nr.: H-20036402). The study is conducted in accordance with the Declaration of Helsinki and written informed consent of parents has been obtained before participation.

## 3. Discussion

Collaboration with the local school health nurses and child dentists could provide an effective structural frame to support behaviour change and anchor new initiatives. However, evidence-based prevention strategies in practice within school health services are still limited [54]. In this multi-component theory-based intervention the effectiveness of disseminating new guidelines on sugar-rich discretionary food and drinks through local school health nurses will be evaluated. The intervention and its wide range of materials will contribute with new insights to this area. The intervention “Are you too Sweet?” has been developed in collaboration with both school health nurses and dentists to suit current practices, thereby ensuring applicability and the likelihood of sustained health-promotion. Further, communication strategies have been developed together with communication partners and tested both through focus groups and in a pilot study to ensure relevance for parents in the target-group.

A high consumption of sugar-rich discretionary food and drinks, especially SSBs, has several health implications, tracking from childhood to adulthood. Prevention of overweight, dental caries and a nutritionally poor diet are concerns that need to be addressed in early school years. Parents as caregivers are the primary role models in shaping their children’s eating habits, and thus, an essential part of the intervention. In recent years, several concepts regarding parenting practices have been developed in relation to family nutritional practices [34,46,50,51]. Systematic reviews have found that control reflected as pressure and restrictiveness have been associated with a higher intake of discretionary food, while parental monitoring and limited home access to discretionary food, have been associated with a lower intake of discretionary food [17,34]. The importance of both accessibility and availability, e.g., as children may not consume fruits and vegetables that are inaccessible, even if available, especially if unhealthy food are also available or accessible, has recently been highlighted [55]. Further, parents acting as positive role models have been associated with lower consumption of SSBs among children, whereas using food as a reward was associated with a higher intake [56]. Qualitative studies have shown that parents face difficulties controlling their children’s intake of sugar-rich discretionary food [57], but also that family eating habits are decisive for the level of intake of sugar-rich food and SSBs [18]. “Are you too Sweet?” encourages parents to both act as role models, as well as limit the availability of sugar-rich food, and make healthy snacks accessible. However, the intervention is limited from structural changes, such as increase in certain tax levels that more directly could enhance changes in accessibility [58].

A strength of this intervention is that the school health nurses are highly experienced in anchoring health initiatives and engaged with parents in shaping healthy habits. Further, joining multiple output data on food intake, anthropometry and a range of behaviour change mediators is a strength of our study design, as hypothetical mechanisms of behavioural change will be discussed. On the contrary, analysis of each mediator might be constrained due to low power. A rather large dropout due to delay caused by the novel COVID-19 virus, has weakened the power, resulting in a change to the study design. Therefore, the randomisation has not been optimal, as one school had to be changed from control school to intervention school [29], and that randomisation had to be performed before baseline measures. The COVID-19 situation might influence peoples eating habits as they stay more at home, and school afternoon snacks are not available, but have to be bought from home. The schools included in this project, do not plan to participate in other health related projects related to the COVID-19 situation.

Further, the allocation status could not be blinded, for obvious practical reasons, for participants or those delivering the interventions. However, randomisation was blinded to the participants until after they completed a 7-day dietary record at baseline. In contrast, a strength is that using current school health services has facilitated that families with different socio-economic backgrounds have been enrolled in the intervention. That said, the representativeness of the study might be reduced because some parents declining to participate, as they reported a lack of sufficient resources to fill out the dietary record and survey. The representativeness will therefore be compared with local data of education and ethnicity when data collection is finished.

The pilot study indicated that the measurement procedures and logistics of the intervention is feasible. However, the pilot study had several weaknesses. Some families had too little time to use and test all materials provided by the project due to the short period. The intervention therefore commenced with only minor changes.

This paper has thoroughly described the development of all components used in the intervention in order to ensure a critical evaluation of all components afterwards. Further, statistical considerations have been described in order to avoid data driven analysis.

